**SCIENTIFIC BACKGROUND**

**1. Why is there a need to investigate the effects of oxygen supplementation after stroke?**

It is now well-established that specialist care on stroke units is effective in preventing death and disability after stroke.[[1]](#endnote-2) It does, however, still remain unclear which aspects of stroke care are crucial for improving outcome. It has been shown that patients on a stroke unit are more likely to receive oxygen than on a non-specialised general ward.[[2]](#endnote-3) Oxygen treatment may thus be a factor relevant to stroke outcome. Mild hypoxia is common in stroke patients and may have significant adverse effects on the ischaemic brain after stroke.[[3]](#endnote-4) While healthy adults with normal cerebral circulation can compensate for mild hypoxia by an increase in cerebral blood flow,[[4]](#endnote-5) this is not possible in the already ischaemic brain after stroke.[[5]](#endnote-6) [[6]](#endnote-7) [[7]](#endnote-8) For all these reasons the use of oxygen treatment is rapidly increasing in European stroke units. A questionnaire survey of UK stroke physicians showed that almost 50% of respondents would start oxygen supplementation after stroke at an oxygen saturation of 95% or above,[[8]](#endnote-9) which is well within the normal physiological range.[[9]](#endnote-10)

There are, however, also reasons for caution. Oxygen treatment is not without side effects.[[10]](#endnote-11) It impedes early mobilisation, poses an infection risk, and may encourage the formation of toxic free radicals leading to further damage to the ischaemic brain.[[11]](#endnote-12) Although in a non-randomised study, the work of Ronning et al have recently suggested that routine oxygen treatment to unselected stroke patients does not reduce morbidity and mortality. Subgroup analyses have further suggested that patients with severe strokes were more likely to benefit than those with mild strokes, but the study size was not sufficient to define patients who are likely to derive benefit.[[12]](#endnote-13) Routine oxygen supplementation for acute myocardial infarction has been abandoned after a clinical trials showed no benefit, and potential harm.[[13]](#endnote-14)

Other than the (non-randomised) study by Ronning suggesting that routine oxygen supplementation of all stroke patients may not be effective there is no evidence from controlled trials to guide oxygen therapy in acute stroke. In particular, there is no genuinely randomised evidence, and therefore no unbiased estimate, of the effectiveness of oxygen supplementation. Recommendations from different Stroke Managemtn guidelines are vague and conflicting.[[14]](#endnote-15) [[15]](#endnote-16) [[16]](#endnote-17) There is great uncertainty amongst physicians treating patients with stroke about which treatment approach to take, and when to give oxygen, as shown by a recent survey of British Stroke Physicians.[[17]](#endnote-18)

For all the above reasons it is important to identify groups of patients who benefit from oxygen, and those who do not.

**What is already known about oxygen supplementation after acute stroke?**

Ronning and Guldvog have suggested that giving oxygen at a rate of 3l/min to all stroke patients during the first 24 hours after hospital admission may not improve overall outcome. However, it is unclear whether this result suggests evidence of an absence of benefit or absence of evidence of benefit. Further, they have not reported baseline oxygen saturation, or changes in saturation on treatment. It is therefore possible that some patients were undertreated, and others achieved too high oxygen levels leading to an increase in free radical generation in the ischaemic penumbra.[[18]](#endnote-19) There are no other data from clinical studies to inform recommendations for the dose of oxygen to give. The recently updated European Stroke Initiative suggests a dose of 2-4 litres/minute,[[19]](#endnote-20) the American Stroke Association Guideline recommends keeping the oxygen saturation at or above 95%,[[20]](#endnote-21) but neither is based on evidence from randomised controlled trials. In the absence of data to the contrary it is reasonable to assume that treatment should aim to restore oxygen saturation to the normal range.

Normal oxygen saturation for adults is 95-98.5%,[[21]](#endnote-22) although in healthy older individuals it is lower at 95%2.5%.[[22]](#endnote-23) In a study of the prevalence of hypoxia in stroke patients conducted in North Staffordshire we have shown that oxygen saturation in stroke patients who are normoxic at recruitment is about 1% lower than that of age-matched community controls.[[23]](#endnote-24) We have just completed a dose titration study for oxygen after acute stroke and found that 2l/min oxygen by nasal cannula increases oxygen saturation by 2% and 3 l/min by 3%.[[24]](#endnote-25) [[25]](#endnote-26)We also found that oxygen masks were less likely to be tolerated than nasal cannulae, leading to poorer treatment compliance with the former. For the proposed study we will therefore give oxygen by nasal cannula. A dosage regime of 3l/min for individuals with a baseline oxygen saturation 93% and 2l/min for individuals with a baseline saturation >93% is likely to prevent hypoxia without increasing oxygen saturation beyond the upper limit of the normal range, and this regime will therefore be used in the proposed study.

There is also no consensus on for how long to continue oxygen supplementation.[[26]](#endnote-27) Data from a local study suggest that the changes in oxygen saturation during the first few days after the stroke cannot be predicted reliably. Over a 3-day period about a third deteriorate, a third remain stable and a third improve.[[27]](#endnote-28) Cells in the ischaemic penumbra may be viable for up to 16 hours in humans,[[28]](#endnote-29) and in baboons an increase in the size of the ischaemic penumbra has been shown between 24 hours and 17 days after the induced stroke, suggesting brain tissue may be at risk of deteriorating long after the ischaemic event. In the only clinical trial of oxygen supplementation after acute stroke published so far oxygen was given for 24 hours, and did not improve outcome.[[29]](#endnote-30) It is possible that a longer duration of treatment may be more effective. For this pilot study a treatment duration of 72 hours has been chosen. This will allow treatment to cover the time when the ischaemic penumbra may still be viable, and the vulnerable period early after the stroke.

# STUDY DESIGN

A randomised controlled open pilot study of routine fixed dose oxygen supplementation versus no routine oxygen treatment.

**DETAILED PLAN OF INVESTIGATION**

**Summary of the study**

This is a study of the effect of routine oxygen supplementation early after acute stroke. A brief synopsis of the trial structure is given in the attached Flow Chart. Subjects will be randomised to receive fixed dose oxygen or no routine oxygen for 72 hours. Oxygen saturation will be recorded over night by pulse oximetry on night 2. The patient will be assessed by a member of the research team on day 3 and week 1 after trial enrolment. At 3 months the researcher will consult the hospital computer system and the patient's notes to find out whether the patient was discharged from hospital and to where. At 6 months after trial enrolment the patient will be sent a questionnaire with questions relating to their daily functional abilities.

**Recruitment**

Patients will be recruited from the University Hospital of North Staffordshire by a member of the research team or the doctor admitting the patient. Because hypoxia is more likely to be detrimental early after the stroke, when the ischaemic penumbra either recovers or expands it is crucial to include patients as soon as possible after the stroke into the trial. Patients will therefore be recruited as soon as they enter hospital via MAU or A&E, if possible, or at the next earliest opportunity up to 24 hours after admission.

# Eligibility for trial inclusion

There are no definite guidelines for oxygen treatment after acute stroke, and there is uncertainty amongst stroke physicians about who should be given oxygen treatment. The eligibility criteria reflect this uncertainty, and allow for randomisation of all acute stroke patients who do not have definite indications or definite contraindications for oxygen treatment.

Adult patients will be eligible for trial inclusion if

- They were admitted with symptoms of an acute stroke within the preceding 24 h
- In the doctor's opinion there is no clear indication for and no clear contraindication against oxygen treatment.
- The patient is able to give consent , or a relative can be contacted to seek assent.

Reasons for not entering patients may include*:*

1. *Recognised indications for oxygen treatment such as* :

- Oxygen saturation on air 90%
- Hypoxia associated with acute left ventricular failure, severe pneumonia and pulmonary embolus
- Chronic respiratory failure treated with long term oxygen at home

1. *Recognised contraindications to fixed dose oxygen treatment (2-3l/min/vy nasal tubes)*

- Type II respiratory failure (contraindication to fixed dose oxygen as given in this trial)

3. *The stroke is not the patient's main clinical problem*

- The patient has another serious life-threatening illness likely to lead to death within the next few months

The final decision for trial eligibility rests with the responsible doctor assessing the patient.

**Diagnosis of stroke**

The diagnosis of stroke will be made by history and clinical examination and is at the discretion of the doctor admitting the patient. It will be based on the WHO criteria (rapidly developing clinical signs of focal (or global) disturbance of cerebral function, with symptoms lasting 24 h or longer, or leading to death, with no apparent cause other than of vascular origin).[[30]](#endnote-31) Within the first 24 hours of symptom onset a definite distinction between a stroke and a transient ischaemic attack cannot be made. However, most patients who still have persistent symptoms after one hour will be confirmed to have a stroke. Since waiting for 24 hours for confirmation would unnecessarily delay treatment we omitted the time element from the definition of stroke for the purposes of trial inclusion

**The uncertainty principle**

Further inclusion and exclusion criteria are not specified precisely, but are guided by the uncertainty principle. If the clinician is convinced (for whatever reason) that the patient should be treated, that patient should not be randomised, but should be given open label oxygen. If the clinician is convinced that (for whatever reason) the patient should not be given oxygen, the patient should not be included in the trial. Only patients who fulfil the inclusion criteria and for whom the clinician is uncertain about the benefit of oxygen treatment should be randomised. The uncertainty principle allows for inclusion of a wide range of patients and the detailed data collection and analysis will enable us to determine and describe the patient group who most benefits from oxygen (in the planned larger study). The uncertainty principle has been successfully used in large trials (e.g. MRC European Carotid Surgery Trial)[[31]](#endnote-32) [[32]](#endnote-33) and is still being used in ongoing stroke trials (e.g. the IST-3 study of thrombolysis for acute stroke currently in progress in our hospital and many others nationally and internationally).[[33]](#endnote-34)

**Intervention**

Patients will be randomised to one of two treatment groups:

1. Treatment group 1: no routine oxygen supplementation during the first 3 days of randomisation.
2. Treatment group 2: oxygen per nasal cannula continuously (day and night) at a flow rate of 3l/min if baseline oxygen saturation is 93% or at a rate of 2l/min (if baseline oxygen saturation 93%) with humidification during the first 3 days after randomisation. Patients who develop definite indications or contraindications for oxygen treatment during the trial will be treated according to clinical need, irrespective of study treatment allocation.

**Blinding**

This study will be open, since placebo treatment (room air via nasal cannulae) would have at least some of the side effects of active treatment (e.g. infection and immobilisation) without any potential benefit, and would thus bias the data in favour of the treatment group. The main outcomes will be ascertained at 6 months by postal questionnaire. It is likely that participants will have forgotten which treatment group they were in 6 months after the intervention, and it is therefore unlikely that treatment allocation will bias their answers. We will assess whether patients remember their treatment allocation by including this as a question in the 6 month assessment questionnaire.

**Consent**

Fully informed consent will be sought from all competent subjects. In subjects who are conscious, but not fully competent to comprehend the information given and make a reasoned decision we will provide a simple explanation of the trial and seek the patient's agreement, but also seek assent from the next of kin. In subjects unable to participate in the decision process in any way we will seek assent of the next of kin only. If an incompetent subject has been included in the trial without giving fully informed consent we will strive to obtain fully informed consent as soon as the patient is able to do so. Consent will be sought by the doctor randomising the patient or by a member of the research team. All doctors randomising patients into the study will be given appropriate information about the trial treatment, potential effects and side effects and the assessment protocol by a member of the research team.

*The reason for including patients who are unable to give fully informed consent*

It is crucially important to include as wide a spectrum of stroke subjects as possible, and, in particular, patients with severe strokes. Patients with severe strokes may be more likely to develop hypoxia, and a recent study has suggested that patients with severe strokes may be more likely to benefit from oxygen than patients with mild strokes. However, patients with severe strokes are more likely to be confused, drowsy or dysphasic and thus unable to give informed consent. Exclusion of subjects unable to give informed consent is thus likely to bias trial outcome.

*The reason for involving the doctor admitting the patient in gaining consent for the study*

There are two major reasons for involving the admitting doctor in the consent process. First, it is likely that any potential neuroprotective effect of oxygen is most pronounced early after the stroke when cells in the ischaemic penumbra are still viable. It is thus important to include patients as soon as possible after admission into the trial to increase the chance of the treatment being beneficial. Second, many emergency units currently prescribe oxygen to stroke patients without good evidence from controlled trials to support this. In the design of this study it is important to match the trial protocol as closely as possible to the therapeutic situation it is designed to assess. While a member of the trial team can be available over the telephone for advice on a 24 hour daily basis, it would be impossible for the researchers to see all potential patients personally on admission. Oxygen is given routinely to patients in the medical emergency department and the medical admissions unit. All doctors know the effects and contraindications, and are thus competent to prescribe oxygen. The research team will make sure that recruiting doctors are aware of the protocol and principles of obtaining consent for research studies.

**Subject/ Patient participation**

This trial does not impose any major risks or burdens upon the patient.

The patient will be given supplemental oxygen via nasal tubes for 3 days or no routine oxygen depending on treatment group. Any patient who develops a definite indication or contraindication for oxygen during the trial will be treated as clinically indicated. Oxygen is widely used and safe in the patient group eligible for study inclusion. We do not expect any major adverse events. Potential minor adverse effects of oxygen are discomfort produced by the nasal cannulae, drying of mucous membranes, and limitation of mobility. On night 2 of the study oxygen saturation will be monitored over night with a pulse oximeter attached to one hand. This may affect the patient's mobility. In most patients the oximeter will be attached to the paralysed hand, and will therefore not interfere with movement. The researcher will ask the patient a few questions on day 3 and examine the patient after one week. This should take a maximum of 5 minutes and does not involve removal of clothes. At 3 months the researcher will consult the hospital records to find out to where the patient has been discharged. At 6 months the patient will be sent a questionnaire asking questions about how the stroke has affected their ability to get on with their daily activities. This may take up to 30 minutes to complete. If the researcher cannot contact the patient by mail or by phone at 6 months they might contact the GP or district nurses to find out how he/she is doing.

**Randomisation and initial assessment**

This assessment is limited to the minimum baseline clinical data required for randomisation and clinical assessment (See Randomisation Form) and incorporates validated tools (Glasgow Coma Scale,[[34]](#endnote-35) [[35]](#endnote-36) Prognostic Factors,[[36]](#endnote-37) and Scandinavian Stroke Scale[[37]](#endnote-38)). This form may be filled in by medial staff in the admissions unit after appropriate training allowing 24/7 recruitment. It is thus kept as short as possible to avoid the randomisation process interfering with clinical care. Any relevant background details which can be retrieved from the notes will be collected by the researcher at the day 3 assessment.

Patients will be randomised by telephone by simple randomisation. We considered using minimisation to balance prognostic characteristics between the treatment and control groups, but decided against this for the pilot since there is a significant chance of guessing trial allocation with this method with a single centre trial.

We are, however, considering treatment allocation by minimisation using well-established factors predictive of stroke outcome (living alone before the stroke, pre stroke functional independence, normal verbal response, ability to lift the affected arm against gravity and ability to walk unaided)[[38]](#endnote-39) and a measure of hypoxia (block 1: baseline saturation 92%, block 2: baseline saturation 93-94%, block 3 baseline saturation 95%) for the planned multicentre trial, and have therefore included the minimisation criteria on the randomisation form.

**Follow-up assessments**

This study is designed to be as simple as possible for the recruiting doctor, to allow patient recruitment to be incorporated into the admission process. All follow-up assessments will be done by a member of the research team.

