**Research Staff**

There will be a full time PhD student (self funding) and a part time research nurse (funded by Geriatric Medicine Research Funds) working on the project.

To allow for 24 hour inclusion of patients by A&E or MAU staff the randomisation procedures are kept very simple. The Trust admits about 2-3 stroke patients per day, and most of those would be randomised by the research team. A&E and MAU staff will only be asked to randomise patients if the unit managers agree with the trial, and if the staff involved are not too busy. While it is expected that the majority of patients will be recruited by the research team, it is considered important for this pilot study, since recruitment by other staff than the core research team will be required for the larger multicentre trial, and any problems with this are likely to become obvious in the pilot phase.

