**Main outcomes**

Comparisons will be made between the treatment and control group to determine:

1. Effect size:

- Death and disability (Rankin >3) at 6 months
- Scandinavian Stroke Scale week 1
- Mortality up to 6 months
- Rankin Score at 6 months
- Nottingham EADL score at 6 months

2. Potential Side effects of the study treatment

- Rate of infections (pyrexia or antibiotic treatment at week 1)
- Agitation (sedative or antipsychotic medication at week 1)
- Physiological indicators of stress (tachycardia, hypertension)

3. To assess the feasibility of the study protocol we will examine

- Protocol violations
- Recruitment rate
- The relation between the number of recruited and excluded patients
- The percentage of completed 6-month questionnaires

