**Stroke Oxygen Study**

# Day 3 Assessment (Assessment form 1)

Name Randomisation no

Pulse oximetry night 2 21:00-9:00 complete Yes No

If pulse oximnetry is not complete, repeat on night 3

Compliance with treatment regimen (tick the statement that applies on day 3)

| Oxygen currently in place (2) | Oxygen not in place, but patient and staff report that the patient is receiving oxygen (1) | No evidence of oxygen supplementation  (0) |
| --- | --- | --- |

Medical History (circle yes or no as appropriate)

| COAD or Asthma [by Hx or from list of drugs] | YES | NO |
| --- | --- | --- |
| Other chronic lung problem [kyphoscoliosis, thoracoplasty, pneumoconiosis etc) | YES | NO |
| Heart failure [by Hx or >20 mg frusemide or equivalent per day] | YES | NO |
| Ischaemic heart disease [H/O angina or MI or tx with nitrates or nicorandil] | YES | NO |
| Atrial fibrillation | YES | NO |

Stroke classification (circle the class that reflects the patient's worst symptoms)

| TAC | PAC | LAC | POC | TIA | Unclassifiable |
| --- | --- | --- | --- | --- | --- |

| Date of pulse oximetry |  |
| --- | --- |
| Baseline wake oxygen saturation |  |
| Mean nocturnal oxygen saturation |  |
| The 4% Oxygen Desaturation Index |  |
| The lowest nocturnal oxygen saturation |  |
| The time spent with an oxygen saturation <95% |  |
| The time spent with an oxygen saturation <92% |  |
| The time spent with an oxygen saturation <90% |  |
| The time spent with an oxygen saturation <80% |  |
| The time spent with an oxygen saturation >98% |  |
| The mean nocturnal heart rate |  |

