**Stroke Oxygen Study**

**Week 1 (Assessment form 2 a)**

Name Randomisation no

Date of death (if applicable)

Please complete the Notification of Death Form if the patient is deceased.

| Antibiotics prescribed since admission | YES | NO |
| --- | --- | --- |
| Continuous oxygen prescribed outside protocol for clinical indications | YES | NO |
| Sedatives or antipsychotic drugs prescribed since admission | YES | NO |
| Highest temperature during week 1 |  |  |
| **The highest heart rate during the 3 days of trial treatment** |  |  |
| **The highest systolic blood pressure during the 3 days of trial treatment** |  |  |
| **The highest diastolic blood pressure during the 3 days of trial treatment** |  |  |
| Highest temperature during week 1 |  |  |

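### The week-1 Scandinavian Stroke Scale is an effect-size outcome, but nothing in the protocol keeps its bedside rater unaware of the allocation

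*Protocol*

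**What the plan says.** Under Main outcomes, the effect-size list includes "Scandinavian Stroke Scale week 1". Two places say who scores it. The Summary of the study states: "The patient will be assessed by a member of the research team on day 3 and week 1 after trial enrolment". Follow-up assessments states: "All follow-up assessments will be done by a member of the research team". Neither sets a condition on what that person may know.

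Research Staff describes the team: "There will be a full time PhD student (self funding) and a part time research nurse". The same section says of the stroke patients admitted that "most of those would be randomised by the research team". The day 3 visit documents compliance with the trial treatment, and its form has the assessor tick whether oxygen is in place.

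The Blinding section makes the study open because room air through a cannula would carry some of the side effects without the possible benefit. On bias it says "The main outcomes will be ascertained at 6 months by postal questionnaire", and adds that patients will probably have forgotten their arm by then.

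**The concern.** The stroke scale is a clinician's rating, and several items need judgement. The arm item separates normal from reduced strength. The speech item separates no aphasia (10) from limited vocabulary or incoherent speech (6), so one step there is worth 4 points. A rater who knows the arm, and expects benefit or harm from oxygen, can lean one way on borderline items without intending to.

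At stake is the credibility of the only listed effect-size measure taken close to the treatment period. The protocol is alert to knowledge of allocation elsewhere: it rejects minimisation because allocation might be guessed in a single centre, and it asks patients at 6 months whether they recall their arm. The week-1 rating has no comparable safeguard. Who rates an outcome, and under what conditions, is a matter for the protocol and is not normally left to an analysis plan.

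**Working it through.** **1. Is the rater likely to know the arm?** Three sections bear on this when read together.
- Research Staff: two staff, and the team randomises most patients, so it receives the allocation.
- Day 3 Assessment (form 1): the team records whether oxygen is in place.
- Summary of the study and Follow-up assessments: the same team scores week 1, with no separation of roles.

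Knowledge of the arm is therefore probable for many patients. It remains an inference, because no sentence says that one individual does all three tasks.

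**2. Does the Blinding section cover this outcome?**
- The placebo-air argument concerns how treatment is delivered. It does not bear on who scores.
- The forgetting argument concerns patients answering a postal questionnaire at 6 months. It does not bear on a staff member scoring at one week.
- The section places the main outcomes at 6 months, whereas the Main outcomes list includes a week-1 rating.

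Neither argument reaches the week-1 scale.

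**3. Is less exposed scoring feasible?** Trial oxygen lasts 72 hours. At day 7 it has been over for 7 − 3 = 4 days, so the trial cannula should no longer be a cue. Other cues can remain (see the objection).

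**4. The plan's own figure.** Study size gives 150 per arm for 0.4 SD with 90% power at a two-sided 5% level, for Rankin, Nottingham EADL and EuroQuol. The normal formula gives n = 2(1.960 + 1.282)²/0.4² = 131.3, so 132 per arm; 150 per arm gives 93.4% power. The stated figure is met with room to spare. It does not concern the stroke scale and this point leaves it unchanged.

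**5. Illustration of what a rater shift would do.** The documents give no SD for the scale and no estimate of rater bias, so the shift b below is an assumption. Take 150 scored per arm, no true effect and a two-sided z test.
- Standard error = √(2/150) = 0.115 SD.
- Rejection rate = 1 − Φ(1.96 − b/0.115) + Φ(−1.96 − b/0.115).

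| Assumed shift b (SD) | Two-sided false-positive rate |
| --- | --- |
| 0 | 5.0% |
| 0.05 | 7.2% |
| 0.10 | 13.9% |
| 0.15 | 25.5% |
| 0.20 | 41.0% |

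The table shows how sensitive the comparison is to a shift. It says nothing about how large the shift would be in this trial.

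**The case against.** The strongest reply is that this is a secondary measure in an openly declared pilot, and that much of what a reader might infer is not in the text. Most of that stands.

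- **That the rater's knowledge is documented.** It is not. Admissions staff may randomise some patients, and the text names only the team. The likelihood comes from two staff and no separation rule.
- **That form 2a takes the rater through the trial oxygen prescription before scoring.** The item reads "Continuous oxygen prescribed outside protocol for clinical indications". Such oxygen can be given in either arm and does not by itself reveal allocation. No order of completion is stated for 2a and 2b; these are page labels. What remains is that completing 2a is likely to send the rater to records from the treatment period.
- **That the bias can be set against 0.4 SD.** That target belongs to other scales, so a ratio to it would mean nothing here.
- **That the multicentre trial would be wrongly sized.** The objectives base its sample size on death and disability at 6 months, and Month 6 assessment makes that the larger study's main outcome. No section uses the week-1 scale for sizing.
- **That nothing at the bedside reveals the arm.** Patients know their treatment and may mention it, oxygen for clinical need may continue, and the study may be explained again at this visit for consent.
- **That the cognitive score is a compromised outcome.** The Mini Mental State is on form 2b but is not in the Main outcomes list.

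Many stroke-scale items also have observable anchors, such as walking 5 m or raising an arm. This limits rater discretion without removing it. None of these replies supplies a blinding provision for the week-1 scale or an argument that one is unnecessary.

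**Conclusion.** The point holds in a limited form. A judgement-based outcome in the effect-size list has no assessor-blinding provision, and the protocol's defence of its open design does not extend to it. That the rater usually knows the arm is likely but inferred. The direction and size of any bias are unknown; the false-positive rates above rest on assumed shifts, 150 scored per arm and no true effect. The 6-month outcomes, the stated study size and the planning of the multicentre trial are untouched. This is an inexpensive improvement to one early outcome and does not undermine the pilot's main purpose.

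**What to change.** In Follow-up assessments and Week 1 assessment, state that:

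1. form 2b is completed before form 2a, and before notes or charts are opened;
2. where possible, form 2b is scored by the research staff member who neither randomised the patient nor completed the day 3 form;
3. patients are asked beforehand not to say which treatment they had;
4. a box on form 2b records whether the rater knew the allocation, to support a sensitivity analysis.

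In Blinding, say that the 6-month argument does not apply to the week-1 scale and refer to these steps.

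The cost is a change of page order, one tick box and a rota rule, with no new staff and no change to sample size, treatment or follow-up. The rota will be constrained because the nurse is part time. If one person randomises and the other does day 3, neither qualifies under step 2, so some ratings will stay unblinded, but they will be flagged. The share flagged would tell the multicentre trial how feasible blinded early rating is.
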